# Evaluating the effects of a risk-adapted screening program for familial colorectal cancer in individuals between 25 and 50 years of age: study protocol for the prospective population-based intervention study FARKOR

**DOI:** 10.1186/s12876-020-01247-6

**Published:** 2020-05-05

**Keywords:** Colorectal cancer, Screening, Family history, Colonoscopy, Fecal blood test, Shared decision making

## Abstract

**Background:**

Colorectal cancer (CRC) is the second most common malignant disease and the second most common cause of cancer death in Germany. Official CRC screening starts at age 50. As there is evidence that individuals with a family history of CRC have an increased risk of developing CRC before age 50, there are recommendations to start screening for this group earlier. This study aims to evaluate the clinical and economic effects of a risk-adapted screening program for CRC in individuals between 25 and 50 years of age with potentially increased familial CRC risk.

**Methods:**

FARKOR (Familiäres Risiko für das Kolorektale Karzinom) is a population-based prospective intervention study. All members of cooperating statutory health insurance companies between 25 and 50 years of age living in a model region in Germany (federal state of Bavaria, 3.5 million inhabitants in this age group) can participate in the program between October 2018 and March 2020. Recruitment takes place through physicians and through a public campaign. Additionally, insurances contact recently diagnosed CRC patients in order to encourage their relatives to participate in the program. Physicians assess a participant’s familial history of CRC using a short questionnaire. All participants with a family history of CRC are invited to a shared decision making process to decide on further screening options consisting of either undergoing an immunological test for fecal occult blood or colonoscopy. Comprehensive data collection based on self-reported lifestyle information, medical documentation and health administrative databases accompanies the screening program. Longterm benefits, harms and the cost-effectiveness of the risk-adapted CRC screening program will be assessed by decision analytic modeling.

**Discussion:**

The data collected in this study will add important pieces of information that are still missing in the evaluation of the effects and the cost-effectiveness of a risk-adapted CRC screening strategy for individuals under 50 years of age.

**Trial registration:**

German Clinical Trials Register, DRKS-IDDRKS00015097.

## Background

Colorectal cancer (CRC) is the third most common malignant disease worldwide, and the second most common cause of cancer death with many cases occurring in developed countries [1]. In Germany, more than 60,000 individuals are diagnosed with CRC every year and about 25,000 patients with CRC die, making it the second most common cancer and the second most common cause of cancer death in Germany [2].

Most cases of CRC develop slowly from precancerous lesions (adenomas). When adenomas or CRC are detected at an early stage, efficient removal and treatment strategies are available. The possibility to prevent CRC through early adenoma removal is an advantage compared to screening and prevention strategies for most other types of cancer [3–5]. Accordingly, there is growing evidence from randomized controlled trials and observational studies that both CRC incidence and CRC mortality can be reduced through screening followed by preventive interventions [4, 6–8].

Over the past two decades, a general decline in the incidence and mortality of CRC has been observed in many countries. At the same time, an increase in CRC incidence in individuals under 50 years is observed in some countries, in particular in the United States [9] and Australia [10].

In Germany, current screening recommendations for the detection of adenomatous polyps and CRC include biennial testing with an immunological test for fecal occult blood (iFOBT) for those aged 50 years and older and colonoscopy every 10 years starting at age 55. However, about 10% of CRC cases are diagnosed before the age of 55. Moreover, there is evidence that individuals with a family history of CRC have a 2- to 4-fold increased risk of developing colorectal carcinoma [11], resulting in a CRC incidence similar to that of individuals without a family history of CRC who are 10 to 15 years older [12]. Despite recommendations to start CRC screening in this group before 50 years of age, there are currently no risk-adapted screening programs for individuals with a family history of CRC in Germany and in many other countries.

To evaluate a screening program, many aspects have to be considered [13]: the prevalence of the disease and its detection rate in the target population, the risks and burdens implied by the program, the risk of overdiagnosis, as well as aspects of costs. While there are estimates on the prevalence of CRC and of precancerous lesions in individuals with a family history of CRC, these estimates may suffer from an inconsistent treatment of individuals with hereditary forms of CRC [11, 14, 15]. There are estimates of the prevalence of having a family history in different countries and ongoing studies estimating this prevalence in Germany [16]. Finally, there is evidence concerning the usefulness of questionnaires to determine family history of CRC in individuals under 50 years of age [17, 18], but data on the compliance and the frequency of adverse effects of CRC screening in a young screening population are scarce. FARKOR aims to provide the missing information to evaluate the clinical and economic effects of a risk-adapted screening program in individuals between 25 and 50 years of age under real world conditions. This article describes the original protocol for the FARKOR (Familiäres Risiko für das Kolorektale Karzinom) study, a prospective population-based intervention study evaluating the effects of a risk-adapted screening program for familial colorectal cancer in individuals between 25 and 50 years of age in the federal state of Bavaria (Germany). Any modifications of the protocol which may impact on the conduct of the study will require a formal amendment of the protocol which will be communicated to all relevant parties.

### Aims and objectives

The study evaluates the effects of the risk-adapted screening program FARKOR, which aims to identify individuals between 25 and 50 years with a family history of CRC and to provide effective, safe and cost effective screening measures for this risk group. In particular, it aims to answer the following primary research question:
Does the prevalence of CRC and of advanced adenoma in the selected risk group justify the use of the proposed screening measures?

Moreover, the study will address the following secondary research question:
Does the introduction of a risk-adapted screening program for individuals between 25 and 50 years lead to a decrease in CRC mortality in this age group?

Finally, secondary research objectives are:
To assess the complication rate of screening colonoscopies in individuals between 25 and 50 years of age with a family history of CRCTo evaluate the compliance of a risk-adapted screening program in the target population by estimating participation rates depending on region, patient characteristics and recruitment by medical specialtiesTo assess the long-term incremental effectiveness and cost effectiveness of FARKOR based on decision-analytic modeling

## Methods/Design

A prospective, population-based intervention study design was chosen to evaluate the effects of FARKOR. All participants will give written informed consent prior to study entry. Recruitment starts in October 2018 and runs until the end of March 2020. First results are expected to be available in October 2020.

### Participants

The recruitment of participants is multimodal. Participating statutory health insurance (SHI) companies^1^ will inform all patients who have been diagnosed with CRC in the last 18 months that their relatives may have a higher risk of developing CRC compared to the general population. The recently diagnosed CRC-patient can inform his/her relatives about the participation in FARKOR. Moreover, physicians will be able to certify for the FARKOR program by undergoing a specific internet based training program on the identification of individuals with a family history of CRC. As FARKOR physician, they recruit subjects between 25 and 50 years of age to participate in the screening program. Finally, there will be a public campaign for the program as well as a website (https://www.darmkrebs-in-der-familie.de/), which allows interested individuals to choose a close-by FARKOR physician.

Inclusion criteria are: Age between 25 and 50 years, membership of a participating SHI, residence in Bavaria, and written informed consent. Individuals for whom adequate CRC related screening measures already exist are excluded from the study. Exclusion criteria are: Previous diagnosis of CRC, familial adenomatous polyposis or chronic inflammatory bowel diseases (ulcerative colitis, Crohn’s disease) or a known family history of hereditary non-polyposis colorectal carcinoma (HNPCC).

### The FARKOR screening process

Participants will be invited by participating physicians to participate in a short standardized interview regarding their family history, which is based on a simplified version of the Amsterdam and Bethesda criteria [20], and to sign a written informed consent form. Based on this short interview consisting of five simple questions concerning the diagnosis of CRC in first- and second-degree relatives, participants are either classified as potential risk carrier if they indicate having at least one first- or second-degree relative with CRC or as risk free. In a shared decision-making, potential risk carriers and their physicians discuss the risks and benefits of possible CRC screening options, which consist of an iFOBT, a screening colonoscopy, or deferring further CRC screening measures to a later point in life. Patients with a positive iFOBT result will undergo diagnostic workup by colonoscopy and both diagnostic and screening colonoscopies are accompanied by a comprehensive documentation of both macroscopic and histologic findings and of potential complications. In case of pathologic findings, patients will receive treatment according to the established guidelines [21]. Additionally, potential risk carriers will be encouraged to undergo an in-depth interview regarding their family history of CRC in which detailed information concerning age, incidence and mortality of CRC in all first- and second-degree relatives is ascertained.

The full FARKOR process is shown in Fig. 1 and consists of the following steps: (1) informed consent, (2) short questionnaire on family history of CRC, (3) shared decision making, (4) offer to complete an in-depth questionnaire on family history of CRC, and (5) further screening measures (iFOBT, colonoscopy, deferral and timing of future screening procedures). All steps in this screening process are accompanied by an internet-based documentation which will be completed by the physicians participating in the program.

**Fig. 1 Fig1:**
[figure not shown]
FARKOR screening process

Additionally to this FARKOR screening process, all participants (with and without family history of CRC) will be invited to complete an online lifestyle questionnaire based on an instrument previously developed for the RAPS study (Risiko-adaptierte Präventions-Strategien für Darmkrebs) [16]. It consists of questions on pre-existing conditions, participation in prevention programs, lifestyle habits (e.g. smoking, alcohol consumption, nutrition, exercise, drug use…) as well as anthropometric and sociodemographic information (including age, sex, height, weight, and educational level).

### Data collection and data protection

The data collection consists of (1) an internet-based documentation of interviews, results of the shared decision-making, and findings of the proposed screening measures, (2) an internet-based lifestyle questionnaire, which is self-administered by the participants, and (3) health insurance data on the incidence of colorectal adenoma and CRC in Bavaria between the years 2015 and 2020. A central trust center will be performing data linkage and pseudonymization. It will also coordinate all requests from participants regarding transparent information, communication and modalities for the exercise of the rights of the data subject according to the EU General Data Protection Regulation (GDPR) including the right to erasure. The analysis will use anonymized data. The analysis dataset will be stored for 10 years following the guideline of good epidemiological practice (GEP) [22].

### Statistical analysis

#### Primary endpoint

The prevalence of CRC (excluding carcinoma in situ) and of precancerous lesions will be evaluated in participants who underwent a screening colonoscopy. Based on health insurance records, it will also be possible to estimate the incidence of CRC and of precancerous lesions (1) in FARKOR participants with familial CRC risk who decide to defer CRC screening measures to a later point in life (2) in FARKOR participants who are classified as risk free, and (3) in individuals in the target population who do not participate in the FARKOR study.

#### Secondary endpoint

The number of complications arising through screening colonoscopies performed in FARKOR will be considered as secondary endpoint.

#### Comparing the prevalence of CRC and of precancerous lesions in study participants to a general screening population

In order to answer the primary research question, the prevalence of CRC and of precancerous lesions in study participants who undergo colonoscopy will be compared to the findings in a screening population of individuals for whom CRC screening is already implemented in Germany. In particular, the findings concerning the prevalence of CRC and of clinically relevant precancerous lesions (advanced adenoma, defined as adenoma ≥ 10 mm, containing high-grade dysplasia, or villous histology) for colonoscopies performed in FARKOR will be compared to the prevalence observed in screening colonoscopies which are proposed to individuals who are aged 55 years and older in Germany.

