### Sample size considerations

The statistical analysis will use a population-based data set. In the sample size consideration, it is only possible to use educated guesses for specific parameters (see Fig. 3). The intervention is implemented in a population of about 3.5 million people (Bavarian population between 25 and 50 years of age) of which about 90% (3.15 million people) are SHI members, who represent the target population. Health care statistics show that about 1.5 million individuals in the target population get in contact with a practitioner or a CRC screening related physician every year. We expect that 90,000 (6% of the 1.5 million) will accept to participate in the program and that 6% of these 90,000 will report a positive family history of CRC. This leads to 5,400 potential risk carriers recruited through contact with physicians. Based on the number of CRC cases in Bavaria, it can be estimated that a further 3,200 potential risk carriers will be recruited through their first-degree relatives who are contacted by their SHI. This results in an expected total of 8,600 participants with a family history of CRC. About 40% will decide for a colonoscopy (3,440). The remaining 60% of these subjects will decide for an iFOBT (5,160) of whom 30% will be positive an undergo colonoscopy (1,548). It is expected that 33% of the colonoscopies will produce findings that result in polypectomy and histology (1,150). Given these numbers, we expect to be able to calculate confidence intervals of fair precision for prevalence of CRC or advanced adenoma (±0.01).

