## Discussion

The Bavarian population of 13 million represents about 16% of the German population. The target population of this study consists of 3.5 million people. We expect to perform about 5000 colonoscopies after shared decision-making of doctors and study participants who are preselected based on a short questionnaire on family history of CRC. It is of interest to see if the prevalence of CRC and of precancerous lesions corresponds to the findings in a screening population of individuals for whom CRC is already implemented in Germany. About 10% of participants in the Bavarian CRC colonoscopy screening program (regularly starting at the age of 55 years) present with advanced adenoma or CRC [30].

Bavaria has also a full coverage by epidemiologic cancer registries. For the target population the registry reports 2065 CRC cases (ICD10 C18-C21) between 2011 and 2014, corresponding to roughly 500 cases per year. It is of specific interest if the selection process via simple questions about the familial colorectal cancer risk is able to find a relevant part of these affected persons. We assume to recruit 8600 individuals who are classified as potential risk carriers in FARKOR. This number is sufficient to allow precise estimates of the prevalence of CRC and of precancerous lesions and to assess essential aspects of the efficacy of the FARKOR screening approach.

It was not possible to implement a comprehensive and systematic process analysis of the program, which could have addressed the following questions in detail: What are facilitators or inhibitors to perform a familial CRC risk assessment? What are reasons that motivate young adults with established familial risk to refuse further active prevention steps like iFOBT or colonoscopy? However, we will address these questions by collecting data concerning a set of potential facilitators and inhibitors including region, medical specialties, and lifestyle factors.

If FARKOR is able to show that the risk-adapted screening program is effective or even cost-effective, there is the option to make it available in whole Germany and to provide a first risk-adapted approach to a familial CRC screening.

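### The primary endpoint is set on screening colonoscopies, but the primary comparison is worded for all FARKOR colonoscopies, which would bring iFOBT-positive work-ups into a prevalence judged against a screening-colonoscopy benchmark

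*Protocol article*

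**What the plan says.** Four places in the protocol article bear on which colonoscopies count.

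- **Primary endpoint.** The prevalence of CRC and precancerous lesions "will be evaluated in participants who underwent a screening colonoscopy".
- **The FARKOR screening process.** The two routes are kept apart: "Patients with a positive iFOBT result will undergo diagnostic workup by colonoscopy and both diagnostic and screening colonoscopies are accompanied" by full documentation of findings. A colonoscopy chosen directly is a screening colonoscopy; one that follows a positive iFOBT is diagnostic.
- **Comparing the prevalence of CRC and of precancerous lesions in study participants to a general screening population.** This analysis is tied explicitly to the primary research question. Its general sentence says the prevalence "in study participants who undergo colonoscopy will be compared to the findings in a screening population". Its specific sentence says the findings "for colonoscopies performed in FARKOR will be compared to the prevalence observed in screening colonoscopies which are proposed to individuals" aged 55 and older. Neither limits the FARKOR side to screening colonoscopies.
- **Sample size considerations and Discussion.** Of 8,600 expected risk carriers, 40% (3,440) choose colonoscopy and 60% (5,160) choose iFOBT, "of whom 30% will be positive an undergo colonoscopy (1,548"). The Discussion gives a total: "We expect to perform about 5000 colonoscopies after shared decision-making of doctors and study participants". It cites about 10% with advanced adenoma or CRC in the Bavarian screening programme as the benchmark.

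**The concern.** The endpoint and the comparison that uses it name different sets of people. The difference matters because iFOBT-positive participants have been pre-selected for lesions, whereas the comparator consists of screening colonoscopies. A prevalence pooled over both routes estimates neither the prevalence in the risk group nor the yield of screening colonoscopy in it. It would also move with the iFOBT positivity rate and with the share choosing iFOBT, and neither of these measures disease burden.

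The primary question is whether prevalence in the selected risk group justifies screening. If the group's true prevalence lies below the benchmark, pooling could make it look equal or higher. With two sets in the text, either could later be defended as the planned one.

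**Working it through.** **Inputs from the article.** Direct colonoscopies 3,440; iFOBT users 5,160; positivity 0.30; polypectomy and histology yield 33%, given as 1,150; precision ±0.01; benchmark about 10%.

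**Assumptions.** iFOBT sensitivity s for CRC or advanced adenoma is not given, so a range is shown. Underlying prevalence p is taken as equal in those choosing colonoscopy and those choosing iFOBT. The confidence level is not stated; 95% two-sided is used.

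**1. The plan's own figures.** The flow reproduces: 8,600 × 0.40 = 3,440; 8,600 × 0.60 = 5,160; 5,160 × 0.30 = 1,548; 3,440 + 1,548 = 4,988, the Discussion's total of about 5000.

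| Denominator | 33% yield | One-third yield | Half-width at p = 0.10 |
|---|---|---|---|
| 3,440 | 1,135 | 1,147 | 0.01003 |
| 4,988 | 1,646 | 1,663 | 0.00833 |

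The half-width is 1.96 × √(p(1 − p)/n). The stated 1,150 fits 3,440 and not 4,988. The ±0.01 also fits 3,440 closely, but 0.0083 rounds to 0.01 too, so 1,150 is the deciding figure.

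**2. Share of work-ups in the set as worded.** 1,548 / 4,988 = 31.0%.

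**3. Effect of pooling.** Lesion carriers among the direct colonoscopies: 3,440 × p. Among iFOBT-positive work-ups: 5,160 × s × p. Hence

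pooled prevalence = p × (3,440 + 5,160 × s) / (3,440 + 5,160 × 0.30).

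| s (assumed) | Factor | True 8% reads | True 10% reads |
|---|---|---|---|
| 0.30 | 1.00 | 8.0% | 10.0% |
| 0.40 | 5,504 / 4,988 = 1.10 | 8.8% | 11.0% |
| 0.50 | 6,020 / 4,988 = 1.21 | 9.7% | 12.1% |
| 0.70 | 7,052 / 4,988 = 1.41 | 11.3% | 14.1% |
| 1.00 (ceiling) | 8,600 / 4,988 = 1.72 | 13.8% | 17.2% |

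The factor exceeds 1 whenever s is above the positivity rate. Positivity is a weighted mean of sensitivity and the false-positive rate, so this holds for any test whose sensitivity exceeds its false-positive rate.

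**4. Against the stated precision.** At a true 8%, the shift is +0.8 points for s = 0.40, +1.7 for s = 0.50 and +3.3 for s = 0.70. The stated half-width is 1 point.

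**The case against.** The strongest reply is that the comparison section is merely shorthand. The Primary endpoint section has already fixed the population, the Secondary endpoint section speaks of screening colonoscopies, and the comparison section never says that the two routes are pooled. The sample-size figures point to direct colonoscopies, the positive predictive value of the iFOBT is already listed as a separate parameter, and a fuller analysis plan, not shown, may name the set. Much of this stands: an intention to pool is not established. But the article itself distinguishes the two kinds of colonoscopy, and the comparison sentence says screening for the benchmark and omits it for FARKOR. Two sections of the same document therefore state different sets for the primary analysis, which is more than a detail left to the analysis plan.

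A reader might infer more than the article supports:

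- **That the sample size rests on all colonoscopies.** It does not: 1,150 matches 3,440, and the two routes are never added in that section. The Discussion's 5000 is a workload total, not a stated primary n.
- **That the bias could reach about 4 points at a true 8% with s = 0.50.** That needs 10% positivity in place of the plan's 30%: 8% × (3,440 + 2,580) / (3,440 + 516) = 12.2%.
- **That the bias could equally be negative under equal prevalence.** With s = 0.25 and 30% positivity at p = 0.08, the false-positive rate would be (0.30 − 0.02) / 0.92 = 30.4%, above the sensitivity. That test is worse than chance.

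It is also fair to object that equal prevalence in the two choice groups is not given, since participants choose their route. If prevalence in iFOBT choosers is r times that in colonoscopy choosers, and positivity stays at 30%, pooling inflates the direct-colonoscopy figure only when s × r > 0.30. At s = 0.50 that means r > 0.60.

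**Conclusion.** The point holds as a conflict between the Primary endpoint section and the comparison section, with bias in the primary comparison if the latter is followed as written. The planning figures for yield and precision side with the endpoint definition, so the comparison wording is the part out of line.

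The direction is upward for any informative iFOBT under equal underlying prevalence. The size cannot be fixed from the article: at the planned 30% positivity, the factor is 1.10 to 1.41 for sensitivities of 0.40 to 0.70, with a ceiling of 1.72. From a sensitivity of about 0.50, the shift at a true 8% exceeds the stated ±0.01 and is enough to bring a group below the benchmark level with it. This should be corrected before results are known, because it affects the one comparison that answers the primary question.

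**What to change.** - In the comparison section, restrict the FARKOR side to direct screening colonoscopies, matching the Primary endpoint section.
- Report findings from colonoscopies after a positive iFOBT separately, alongside the positive predictive value already planned, and do not pool them against the benchmark.
- In Sample size considerations, state that the 33% yield and the ±0.01 refer to n = 3,440.

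The cost is about one sentence in each place. The half-width at 10% prevalence is ±0.0100 rather than the ±0.0083 of the pooled set, which still meets the stated ±0.01 (exactly 0.01 would need n = 3,458). The restriction does not remove self-selection into colonoscopy; it makes the two sides of the comparison the same kind of examination.
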